### Process evaluation

Consistent with Medical Research Council (MRC) guidance for trials of complex interventions, we will conduct a process evaluation [59]. This evaluation aims to explore the fidelity of implementation, mechanisms of impact, and contextual factors that facilitate or impede intervention delivery. We will pay particular attention to documenting and analyzing contextual variations across clusters (e.g., socio-cultural characteristics, access to health services). This will complement the outcomes evaluation through exploring: (1) fidelity of intervention delivery by different researchers; (2) participants satisfaction with treatment; (3) adherence rates; (4) dropout rates; (5) participants’ experience of the integrated intervention, including perceived benefits, facilitators, barriers, and any unexpected consequences; and (6) identify contextual factors across different clusters and explore the role in shaping the implementation process of intervention.

### Statistical analyses

Analyses will include descriptive summaries and preliminary unadjusted comparisons between phases (control vs. intervention) and clusters. Specifically, variables within each phase or clusters will be described using descriptive statistics (means and 95% confidence intervals for normal distributed quantitative variables; medians and interquartile ranges for non-normally distributed quantitative variables).

Analyses of data from a SW-CRT requires specific methodological considerations to account for its design, including the control of secular trends (period effects) and the assessment of potential carryover effects. Guided by methodological recommendations for SW-CRTs [60], we will choose Method 3 to evaluate the intervention effects of the integrated exercise-sleep intervention. This method treats the intervention variable as a time-dependent categorical variable, comparing groups with different numbers of intervention measurements with all the control measurements. This allows us to examine whether the effect of the integrated exercise–sleep intervention varies with the length of exposure, thereby informing the time dependency of treatment effects, including potential carryover.

All models will be estimated using multilevel mixed-effects regression to account for the hierarchical structure of the data. We will first fit a two-level (time and individual levels) and a three-level (time, individual, and community levels) mixed-effects model without any potential confounders. Then, we will further adjust the selected model (based on model fit criteria) by including study period (time) as a fixed effect. Third, an adjustment will be made for the baseline value of the outcome variable and associated baseline covariates (e.g., socio-demographics, cognition), and in the fourth step, both an adjustment for the follow-up time, the baseline value of the outcome variable, and related covariates will be performed. To evaluate the time dependency of the effect of starting the intervention, an interaction term between intervention and time can be added to the model [60, 61]. Additionally, we will account for potential between-cluster variations by including relevant community-level covariates (e.g., socio-cultural characteristics and access to health services) as fixed effects in the models, if they show preliminary associations with the outcome.

The economic evaluation will include both cost-effectiveness analysis (CEA) and cost-utility analysis (CUA), considering only costs and effects occurring within the trial timeframe. CEA will assess the intervention effect on depression symptoms relative to costs in older adults. Results will be expressed as cost-effectiveness ratio (CER) and incremental cost-effectiveness ratio (ICER). CUA will be calculated by QALYs and cost-utility ratio (CUR). For the exploratory analyses of mechanistic outcomes, we will examine the intervention effects on the biomarkers (i.e., salivary BDNF and irisin levels) from baseline to post-intervention. Analyses of EEG data will be conducted on the subset of participants who complete this assessment and are therefore exploratory in nature. We will compare baseline characteristics between participants who do and do not complete the EEG to assess potential selection bias. Indicators including absolute power (AP), phase locking value (PLV), phase lag index (PLI), and weighted phase lag index (WPLI) will be analyzed to investigate potential neurophysiological mechanisms underlying the intervention’s effectiveness.

Primary analysis will follow the intention-to-treat (ITT) principle, including all randomized participants. Primary and secondary outcomes will be performed with generalized linear mixed models (GLMMs). Estimated intervention effects will be reported as mean differences for continuous outcomes or odds ratio for binary outcomes between intervention and control periods. To handle missing outcome data, we will employ multiple imputation by chained equations (MICE) under the assumption of missing at random. Sensitivity analyses will be conducted to assess the robustness of the findings by: (1) comparing results from the ITT analysis with those from a per-protocol (PP) analysis; (2) evaluating the impact of missing data under different assumptions (e.g., missing not at random scenarios); (3) adjusting for baseline depression symptom severity; and (4) using different depression classifications (i.e., the total score of PHQ-9 or the diagnostic criteria for depression based on DSM-IV [30, 62]). All analysis will be performed by an independent statistician using R software version 4.3.2 (R Core Team, R Foundation for Statistical Computing, Vienna, Austria, https://www.R-project.org). Statistical significance will be defined as a two-tailed *p*-value < 0.05.

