### Randomization and blinding

Initially, all six communities will begin in the control phase. Subsequently, two communities will be randomly allocated to the 12-week intervention period, followed by two other communities 12 weeks later, and the final two communities 12 weeks after that. Trial randomization will be performed by an independent researcher not otherwise involved in the study. Each community will be notified of its own transition date after recruiting first participant but will not be notified of the transition dates of other communities. Details of the randomization schedule are given in Fig. 1.

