### Sample size

Power calculation was performed using the PASS software module ‘Tests for Two Means in a Stepped Wedge Cluster Randomized Design’. Key input parameters were derived from a similar previous study [47], which reported a mean reduction in depressive symptom of 4.0 in intervention group compared to 2.0 in control group among community-dwelling older adults with depression. Based on our stepped-wedge design with 6 clusters, 2 clusters crossing over per sequence, an intra-cluster correlation (ICC) of 0.1, a planned sample size of 22 per community, a desired power of 90%, a two-side α level of 0.05, and an estimated 20% dropout rate, a total sample size of 165 participants will be required.

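### The 90% power is for one constant intervention effect, but the chosen Method 3 gives a separate effect per number of intervention measurements and none is named primary

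*Protocol article*

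**What the plan says.** **Sample size.** Power comes from the PASS module "Tests for Two Means in a Stepped Wedge Cluster Randomized Design". The effect is one difference, a "mean reduction in depressive symptom of 4.0 in intervention group compared to 2.0 in control group", so 2.0 points. The design is a "stepped-wedge design with 6 clusters, 2 clusters crossing over per sequence", with ICC 0.1, two-sided 5% and "a planned sample size of 22 per community, a desired power of 90"%. Allowing for 20% dropout, the total is 165.

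**Statistical analyses.** Method 3 is selected for evaluating the intervention and described thus: "This method treats the intervention variable as a time-dependent categorical variable, comparing groups with different numbers of intervention measurements with all the control measurements". Its stated purpose is to see whether the effect changes with duration of exposure, including possible carry-over. The same section later says: "Estimated intervention effects will be reported as mean differences for continuous outcomes or odds ratio for binary outcomes between intervention and control periods".

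**Measurement of outcomes and Table 1.** The primary outcome is the PHQ-9 at 12 weeks. Table 1 schedules the PHQ-9 at baseline, 6 weeks and 12 weeks, with no later visit.

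**Randomization and blinding.** All communities start in the control phase. Then "two communities will be randomly allocated to the 12-week intervention period", with the next pairs following at 12-week intervals.

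**The concern.** The power calculation and the analysis address different quantities. A two-means stepped-wedge calculation assumes that the effect is the same at every intervention measurement, so all intervention cells inform one parameter. Method 3 splits that parameter by exposure level. Later levels rest on fewer communities and are harder to separate from period effects. A reader would carry the 90% over to whichever Method 3 coefficient is reported, and with none designated the choice could be made after the results are known.

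There is also a question of interpretation. Every participant receives a 12-week programme. If measurements continue beyond 12 weeks after cross-over, the higher levels describe persistence or fading after the programme has ended. Reading them as an effect of longer exposure would mislabel a waning effect.

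**Working it through.** **1. Reproduce the stated total.** 6 × 22 = 132, and 132 / 0.8 = 165. This agrees.

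**2. Inputs for power.** From the Sample size section: difference 2.0, ICC 0.1, 6 communities, 2 per sequence (3 sequences), two-sided 5%. With a common control start and 12-week steps this gives 4 periods. That grid is inferred, because the schedule is in Fig. 1, which was not available for this check. The article gives no SD and does not say whether 22 is per period or in total, so the 90% cannot be reproduced directly. The SD was instead solved so that the constant effect has exactly 90% power, and the same design was then analysed with Method 3.

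**3. Formulas.** Generalised least squares on community-period means, with fixed period effects:

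- Constant effect: mean(i,j) = β_j + θ·X_ij, where X_ij = 1 after cross-over.
- Method 3: mean(i,j) = β_j + δ_s, where s = 1, 2 or 3 is the number of intervention periods so far and δ = 0 under control.
- With V the 4 × 4 covariance of a community's period means and D_i its design matrix, the covariance of the estimates is (Σ D_i′ V⁻¹ D_i)⁻¹.
- Power = Φ(2.0/SE − 1.960).

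**4. Calibration.** 90% power needs SE = 2.0 / (1.960 + 1.282) = 2.0 / 3.242 = 0.617 for the constant effect.

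**5. Method 3 under the same design and SD, with a true effect of 2.0 at every level.**

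| Reading of 22 | SD giving 90% (constant effect) | SE, levels 1 / 2 / 3 | Power, levels 1 / 2 / 3 | Power, equal-weight average |
|---|---|---|---|---|
| 22 per community-period, different people | 4.05 | 0.658 / 0.949 / 1.371 | 86% / 56% / 31% | 59% |
| 22 per community in total (5.5 per period) | 2.13 | 0.636 / 0.883 / 1.253 | 88% / 62% / 36% | 68% |
| Cohort of 22, within-person share 0.5 | 5.64 | 0.668 / 0.975 / 1.416 | 85% / 54% / 29% | 56% |

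Example for row 1, level 2: 2.0/0.949 − 1.960 = 0.147, and Φ(0.147) = 0.56.

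The joint 3-df test has 78% power in each row. The levels are informed by 6, 4 and 2 communities respectively.

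**6. Sensitivity.** Further variants took within-person share 0.3 and 0.7, 27.5 per community-period, and cluster autocorrelation 0.8. Across all variants the ranges are about 85-88%, 53-64% and 29-37% for the three levels, and 55-70% for the average. The standard errors are about 1.03-1.09, 1.40-1.60 and 1.98-2.32 times that of the constant effect. The shortfall relative to the constant effect therefore does not hinge on the unstated SD.

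**The case against.** **The 12-week time point already points to one level.** On the 12-week grid it is level 1, where the loss is only 2-5 points. This stands, and it limits the size of the problem. But 12 weeks is the first intervention measurement on the step grid and the second if the 6-week visit counts, and the article does not say which.

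**The three-level grid may not arise.** Table 1 lists no PHQ-9 after 12 weeks, so the levels could be the 6-week and 12-week visits, both within the programme. If 6-weekly measurements in both phases entered the model, the 12-week effect would have about 92-93% power. This is a fair reading. However, those measurements are not among the stated power inputs, and the coefficient is still not named.

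**The reporting sentence need not conflict with Method 3.** It speaks of effects and differences in the plural, and each Method 3 coefficient is an intervention-versus-control difference. Accepted: the gap is the missing designation, not a flat contradiction. Carry-over is also named as a purpose of Method 3, though it is not separated from duration of exposure.

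**Without period effects, power is far higher** (at least 99%, 96% and 78% for the three levels). That model omits the secular trend which the article itself says must be controlled.

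**The SD and correlations belong in the full protocol or SAP.** Accepted. Their absence from an article is not the point raised here.

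**A stronger reading to avoid.** A reader might infer that 90% is reachable only with an SD near 4.0 and 22 new people per community in every period (22 × 6 × 4 = 528). The documents do not support this. A cohort of 22 per community with within-person share 0.5 reaches 90% at SD 5.64. At SD 4 and cluster autocorrelation 1, following the same people raises constant-effect power from 90.6% to 99.5%.

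**Conclusion.** The point holds as a mismatch between the stated power and the stated analysis. The 90% belongs to one constant difference, whereas the selected method produces several effects with no primary one designated. If the constant effect has 90% power on a 12-week grid, the first level has about 85-88%, the second 54-62%, the third 29-36% and the equal-weight average 56-68%. The stated power is thus nearly right for the first level and wrong for the later levels and the average.

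A reader might go further and conclude that the trial is underpowered for its primary question, or that the primary effect is wholly undefined. Neither follows: the outcome and its time point are fixed, and the low figures belong to levels that no section calls primary.

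The figures assume the inferred four-period grid, a true effect of 2.0 at every level and a normal approximation, which is optimistic with six communities. That higher levels are post-programme is conditional on measurements being taken more than 12 weeks after cross-over.

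**What to change.** In the Statistical analyses section:

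- Declare one primary contrast: the period-adjusted effect at the end of the 12-week programme versus control.
- State which Method 3 coefficient this is, and how the 6-week visit is counted.
- Label any later measurements as secondary post-programme or carry-over effects, and do not interpret them as longer exposure.

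In the Sample size section:

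- Say that the existing 90% refers to a constant effect.
- Restate the power for the primary contrast under the repeated-measures cohort design, over a stated range of SD, within-person correlation and cluster autocorrelation.

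The cost is wording plus one recalculation, with enrolment unchanged. The restated power may come out below or above 90%, depending on the SD and correlations. The choice of contrast should be fixed before outcome data are analysed.

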### Ethical approval and protocol registration

This study was approved by the Ethics Review Committee of Xiangya School of Nursing, Central South University (No. E2025144). The trial protocol was registered on www.chictr.org.cn (Registration number: ChiCTR2500107641) prior to the recruitment of the first participant. The study will be conducted in accordance with ethical principles, including obtaining written informed consent from all participants during the baseline assessment. All researchers have signed confidentiality agreements. Upon completion of study participation, participants will receive an acknowledgment letter and 100 CNY as compensation for their time.

## Discussion

Both empirical evidence and theoretical underpinnings underscore the significant roles of exercise and sleep health in maintaining physical and psychological health. Targeting both should alleviate depressive symptoms, improve quality of life and physical health. The GESO project therefore aims to evaluate the effectiveness and cost-effectiveness of a home-based, integrated exercise-sleep intervention for depressed community-dwelling older adults using a SW-CRT study design.

To our best knowledge, this is the first study incorporating a cost-effectiveness analysis of an integrated exercise-sleep intervention for this population. Several lines of results are anticipated from this study. Our intervention was tailored for depressed older adults through a multi-step process involving cognitive interviewing, pilot testing, and expert consultation, incorporating identified facilitators and barriers. Regarding the delivery format, this study evaluates a home-based integrated intervention. This contrasts with most RCTs where the training is typically conducted in group sessions under the supervision of an instructor outside the home environment. The home-based format enables researchers to provide extensive expert-validated online resources (text, images, videos), and is potentially more cost-effective. For outcome evaluation, cost-effectiveness analysis and cost-utility analysis will be conducted from a public health service perspective. These analyses will highlight the intervention’s significance and assess its potential for scalability. Regarding mechanisms of effectiveness, we plan to explore the underlying mechanisms by analyzing EEG-derived functional connectivity along with salivary levels of BDNF and irisin.

There are some limitations in this study. First, although the proposed SW-CRT design has several advantages over parallel group RCTs, it is not as methodologically rigorous as a true cluster-randomized design, and inevitably brings challenges in recruitment and implementation [63], possibly create time contamination and complexity of analysis. Nevertheless, recruitment of the GESO project will be community-based participatory research, that is, community organizations will contribute to both the recruitment and implementation phases of the project through activities such as promotion and participant mobilization, assistance with follow-ups, and the provision of venue resources. Second, this study design precludes the effectiveness evaluation of the core active components or optimal strategies compare with overall intervention package. For instance, it cannot determine the optimal sequence for delivering exercise versus sleep intervention or evaluate the potential of alternative delivery agents (e.g., virtual agents, primary care nurses, non-specialist assistants). Future studies could employ a sequential multiple assignment randomized trial (SMART) design to optimize strategies and test such alternative agents. Third, the collection of EEG data is optional and require additional time (e.g., commuting time) for participants, which is likely to result in a subsample of participants with greater motivation or better physical mobility. Therefore, the findings of EEG should be interpreted as preliminary and may not generalize to the full study population. Finally, culturally and linguistically diverse residents are likely to be underrepresented, due to constraints in financial and human resources, which may limit the generalizability of the results. Further multicenter studies recruiting a wider range of older adults with larger sample sizes are recommended.

In conclusion, the present study will advance the extant knowledge about effectiveness, acceptability, and cost-effectiveness of an integrated exercise-sleep intervention, with a specific focus on older adults with depression in community settings. The findings will contribute to providing a more cost-effective, evidence-based, and scalable lifestyle intervention for this population.

### Data Availability

The datasets generated during the present study can be obtained from the corresponding author on reasonable request, respecting the participant confidentiality. The trial results will be communicated via publications.

## Data Availability

The datasets generated during the present study can be obtained from the corresponding author on reasonable request, respecting the participant confidentiality. The trial results will be communicated via publications.
